## **9.3 Procedures at Each Visit**

### **9.3.1 Screening**

Screening will be done via telephone. The study center will clarify the basic inclusion criteria (see S1: demographic data, back pain duration and severity ( $\geq 4$  NRS), acupuncture treatment experience, known pregnancy as reported by the patient). In case the patient is interested, fulfills the inclusion criteria and does not fulfill any exclusion criteria, the informed consent form for Study Phase 1 (S4, which includes the informed consent only for the baseline questionnaire data) and the baseline questionnaire (P1) will be mailed to the patient. The patient information will be collected on a sheet (S5), which will be saved separately from other documents in a locked container with defined access.

The patient will be asked to read the documents, sign the informed consent and bring the signed consent together with the completed baseline questionnaire to the first visit with the physician. All visits will be scheduled with the patient and documented on S3.

### **9.3.2 Baseline (Visit 1a)**

The first visit will take place at the Institute of Complementary and Integrative Medicine. The patient will be asked to hand in the informed consent for study phase 1 he had signed after the telephone interview and the baseline questionnaire to the study center. The study center will check them for completeness.

From the physician, the patient will receive the patient information for study phase 2 (B2) and will be asked to read it carefully.

Thereafter, the physician will inform the patient in detail about the study. The patient will have the opportunity to ask questions concerning the second phase of the study. The second informed consent will be given to the patient and he will be asked to read and sign it if he or she is still interested to participate in the study.

The physician will then check the inclusion criteria (See B1: demographic data, pain duration and severity ( $\geq 4$  NRS), health status and patients' medical history/comorbidity).

The appointments fixed at the first phone screening will be provided to the physician by the study center. The physician and the patient will go through all the appointments to confirm that the patient can come for acupuncture on all dates.

In case of inclusion, the physician will assign the patient to a group allocation via secuTrial.

Afterwards, the briefing will take place for around 30 minutes. In the course of this briefing, material will be provided to the patient to take home (see brochures).

In addition the physician will give the patient the EAT (P2) and CARE (P4) and ask him to complete them immediately and to hand out P2 and to put P4 into an envelope. The physician will meanwhile fill in the adherence questionnaire B4.

### **9.3.3 First acupuncture (Visit 1b)**

After the briefing, the patient will receive the first acupuncture.

After the acupuncture, the rescue medication weekly diary (P6) for week 1 will be handed out and explained to the patient. At the end, the acupuncturist will fill out the adherence questionnaire A1, the patient the acupuncturist's alliance (P5).

### **9.3.4 Visit 2**

The second visit should take place within 2-7 days after the first acupuncture session. Before the second visit, participants will experience their booster session (according to the group allocation), which will take ca. 15 minutes (10 minutes effectiveness briefing and 5 minutes

safety briefing) and will be guided by the physician who also did the initial briefing session. The physician will again fill out the adherence questionnaire B5.

At the beginning of the acupuncture session, the side effects (P9) of the last acupuncture session will be measured and the weekly rescue medication diary (P6) will be checked. Patients will then receive the second acupuncture treatment.

After the session, the acupuncturist will fill out the adherence questionnaire A2.

### **9.3.5 Visit 3**

This will be the third acupuncture session, which should take place within 2-7 days after the second acupuncture session. At the beginning, the side effects (P9) will be measured and the rescue medication diary (P6) will be collected. The patient will receive a new sheet and will be told to continue the diary for week 2.

Patients will then receive the acupuncture treatment.

Thereafter, the acupuncturists will fill out the adherence questionnaire A2.

After this session, the participant will receive the email/letter booster according to the group allocation.

### **9.3.6 Visit 4**

Session 4 will be in the mid of the acupuncture treatment phase and hence, EAT (P2), PROMIS (P3) and NRS (P7) will be assessed after this session in addition to the normal session flow.

### **9.3.7 Visit 5-8**

Sessions 5 to 8 will be the final four acupuncture sessions, which take place within 2 weeks. Each time, side effects and rescue medication diary will be recorded or checked, respectively, before the acupuncture starts. After visit 6, the patients will again receive an email/letter booster as after visit 3. After the very last acupuncture session (visit 8), the acupuncturist will answer the post-treatment questionnaire (A3) and the patient will fill in the acupuncturist's alliance questionnaire (WAI-SR, P5). Moreover, pain (P7), PROMIS (P3) and PSM (P8) will be assessed.

### **9.3.8 Follow up (Visit 9)**

Six months after the last visit, patients will again be contacted and asked to fill out the follow up questionnaire (P12) including NRS (P7) and PROMIS (P3). They will receive the questionnaire by mail and will be asked to send it back to the study office in the prepaid questionnaire.

### **9.3.9 Study end (Visit 10)**

The patient will be informed about the study aim and the patient information and the informed consent for study phase 3 will be handed out (B6). The patient can then withdraw his or her informed consent or sign the third consent form. The patient will be asked for a post-treatment guess about the group allocation (P10).

## 10 SAFETY

The Sponsor's SOPs provide more detail on safety reporting.

During the entire duration of the study, all serious adverse events (SAEs) that may be causally related to the study intervention are collected and documented in source documents. Reportable events are recorded in the case report form (CRF). Study duration encompassed the time from when the participant signs the informed consent until the last protocol-specific procedure has been completed, including a safety follow-up period.

In accordance with ClinO, serious adverse events (SAEs) are to be documented in a standardized manner and reported to the CEC if it cannot be excluded that the events are attributable to the intervention under investigation.

Furthermore, we will document adverse effects (= side effects of acupuncture treatment) (primary outcome for hypothesis 2) that might occur after each acupuncture session (assessment before the next acupuncture session).

### 10.1 Definitions

#### **Adverse Effects (= side effects)**

All unintended responses to a medicinal procedure related to any dose should be considered adverse effects. The phrase "responses to a medicinal procedure" means that a causal relationship between a medicinal procedure and an adverse effect is at least a reasonable possibility, i.e., the relationship cannot be ruled out.

For acupuncture we will especially focus on those side effects:

- bleeding at the injection site during acupuncture
- Bruises at the injection site after acupuncture
- Pain during acupuncture
- Inflammation at the injection site
- Vegetative symptoms such as
  - dizziness
  - transpiration
  - tachycardia
  - nausea
  - blood pressure problems
  - fatigue
- reinforcement of back pain
- Other pain (e.g. headaches or local muscle pain)

#### **Serious Adverse Event**

A serious adverse event is defined as any event which:

- requires inpatient treatment not envisaged in the protocol or extends a current
- hospital stay;
- results in permanent or significant incapacity or disability;
- is life-threatening or results in death; or
- causes a congenital anomaly or birth defect.

## 10.2 Recording and Assessment of Serious Adverse Events

The investigator has the responsibility for SAE identification, documentation, and assessing the causal relationship study intervention.

All SAEs will be fully documented in the appropriate CRF for up to 4 weeks after the intervention. At the last visit, patients will be instructed to report any SAE that occur within the next 4 weeks. For each SAE, the investigator will provide the onset, duration, treatment required, outcome and action taken with regard to the study intervention.

The assessment by the investigator with regard to the study intervention relation is done according to the following definitions:

|                  |                                                                                                                                                                                                                                                 |
|------------------|-------------------------------------------------------------------------------------------------------------------------------------------------------------------------------------------------------------------------------------------------|
| Unrelated | 

• The event started in no temporal relationship to the medical intervention applied and

• The event can be definitely explained by underlying diseases or other situations.

             |
| Related   | 

• The event started in a plausible temporal relationship to the medical intervention applied and

• The event cannot be definitely explained by underlying diseases or other situations.

 |

## 10.3 Reporting of Serious Adverse Events

If, in the course of a clinical trial, serious adverse events occur in participants in Switzerland, and it cannot be excluded that the events are attributable to the intervention under investigation, the investigator must report these events to the CEC **within 15 days**.

### Safety and protective measures

If immediate safety and protective measures have to be taken during the conduct of this clinical trial, the investigator must notify the CEC of these measures, and of the circumstances necessitating them, **within 7 days**.

### Annual Safety Report

All SAEs will be summed up in the **annual safety report (ASR)** and submitted to the CEC. ASR shall contain:

- A summary of events including severity and causal relationship to the intervention and on the safety of participants.
- The accompanying letter provided with the Annual Safety Report should contain a short summary of the status of the clinical trial in Switzerland (number of centers open/closed, number of patients recruited/recruitment closed, and number of SAEs).

## 10.4 Follow up of (Serious) Adverse Events

Participants terminating the study (either regularly or prematurely) with reported ongoing SAE will return for a final follow-up investigation. This visit will take place up to 30 days after terminating the treatment period. Follow-up information on the outcome will be recorded on the respective SAE page in the CRF.

Follow-up investigations may also be necessary according to the investigator's medical judgment even if the participant has no SAE at the end of the study. However, information related to these investigations does not have to be documented in the CRF but must be noted in the source documents.

## 11 STATISTICAL METHODS

### 11.1 Hypotheses

#### 1) Effectiveness

We will test the null hypothesis:

(1a) high expectation briefing = regular expectation briefing for change in expectation

The alternative hypothesis is:

(1a) high expectation briefing  $\neq$  regular expectation briefing for change in expectation

We will test the null hypothesis:

(1b) high expectation briefing = regular expectation briefing for back pain,

The alternative hypothesis is:

(1b) high expectation briefing  $\neq$  regular expectation briefing for back pain

We use this hierarchical test procedure to control for multiple testing. In a first step, we will test if the briefing changes the expectation. Only if the null hypothesis 1a was rejected (high expectation briefing  $\neq$  regular expectation briefing) we will test in a second step whether the briefing changes pain after treatment (hypotheses 1b), using the same alpha level.

#### 2) Side Effects

We will test null hypothesis:

(2) high side effect briefing = regular side effect briefing for amount of side effects reported

The alternative hypothesis is:

(2) high side effect briefing  $\neq$  regular side effect briefing for amount of side effects reported

### 11.2 Determination of Sample Size

For sample size calculation we used nQuery Advisor (version 7.0).

Research question 1a: No previous data on expectancy change were available for trial planning purposes. For this study, we assume that the high expectation briefing is clinically meaningful better than a regular expectancy briefing in changing expectation, with a standardized mean difference (SMD) 0.5.

Assuming a power of 80% and a two-sided alpha level of 5%, we calculated that a sample of 128 patients (64 high expectation briefing and 64 regular expectation briefing) would enable detection of a difference of SMD 0.5 for the expectancy briefing intervention. Assuming a dropout rate of approximately 15%, we sought to enroll 150 patients.

Research question 1b: With the above mentioned sample we will have a power of 56-65% (n=128-150) to detect a significant difference between high and regular expectation briefing on average pain severity after 4 weeks. This assumption is based on our previous study

(Linde et al., 2007) with response rates of 54% in the high expectation group and 39% in the low expectation group that resulted in an SMD of .38.

Research question 2: Variation of the outcomes was not known prior to the study. Thus, the sample size was determined using two-group Fisher's exact tests of equal proportions (for binary outcomes). We expected to have 50% of patients with side effects to calculate a side effect score in the safety briefing group and 10% in the group without intense safety briefing (Witt et al., 2009). It showed that with 64 patients in each study group such differences in outcome scores could be detected with at least 99% power at a .05 two-sided significance level. This power analysis was conservative and the actual power of the study will be higher since we will use a continuous score and not only a binary variable.

## **11.3 Planned Analyses**

### **11.3.1 Datasets to be Analyzed, Analysis Populations**

The analyses will be tested for the intention to treat population using all available data.

Group allocations (briefing interventions):

- High expectancy vs. regular briefing
- Intense side effects briefing vs. regular side effects briefing

Measurement time points (data acquisition during the experiment):

- Baseline
- After 2 weeks
- After 4 weeks
- 6-months follow-up
- Study end

### **11.3.2 Primary Analysis**

The significance level will be set to  $\alpha = .05$ . It will be tested two-sided.

For the first hypotheses (1a) we will use an analysis of covariance (ANCOVA) with the fixed effects briefing group and sex and the covariate baseline expectation to determine the difference on expectation (EAT score) before the first acupuncture treatment between both briefing interventions.

For the second hypotheses (1b) to determine the difference in pain (numeric rating scale) after 4 weeks of acupuncture treatment we will use ANCOVA with the fixed effects briefing group, sex, therapist and the covariates baseline pain and optimism.

We use this hierarchical test procedure to control for multiple testing. In a first step, we will test if the briefing changes the expectation. Only if the null hypothesis 1a was rejected (high expectation briefing  $\neq$  regular expectation briefing) we will test in a second step whether the briefing changes pain after treatment (hypotheses 1b), using the same alpha level.

Sensitivity analyses for both analyses will include a.) adding various covariates to the model (e.g. age, duration of disease, depression, empathy), b.) changing the study populations (per-protocol), and c.) using different multiple imputation methods for missing data (hot deck and regression methods). Confidence intervals and p-values from sensitivity analyses are

considered explorative. The research question if briefing effects on pain are mediated by initial treatment expectations will be tested according to the framework suggested by Baron and Kenny (Baron & Kenny, 1986; Hayes, 2009) in a hierarchical regression analysis.

Research question 2: As primary analysis, the total side effect score after 8 sessions will be compared between safety briefing groups using zero-inflated and hurdle models for count data. This analysis will require to appropriately imputing intermittent missing side effect scores and dropouts. Alternatively, a longitudinal analysis of the side effect scores, available from up to 8 sessions, will be achieved through an appropriate model extension using patient-specific random effects. As no standard software is available for this, problem-specific implementation using Markov Chain Monte Carlo (MCMC) or INLA ([www.r-inla.org](http://www.r-inla.org)) will be used. Analyses will be conducted after LPLV by the statistician, presumably in the third year of the project.

In addition to the above mentioned research questions as an exploratory analysis for the total sample of included patients independent of group allocation to briefings the pain will be predicted by patient expectation before treatment using regression analyses with baseline pain severity, age, and sex as covariates. For the outcome pain two time points are relevant: 1) pain after 4 acupuncture sessions for the short term impact of expectations; 2) pain after 8 acupuncture sessions for the total impact of expectations on treatment outcomes.

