## 4 Statistical Principles

### 4.1 Confidence Intervals and $p$ -Values

All confidence intervals are 95% and two-sided. All tests are two-sided and performed at a significance level of 0.05.

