### 6.5 Missing Data

The analysis will require to impute missing values, intermittent missing side effects scores, and dropouts.

The distribution and pattern of missing values will be assessed using tables and plots (using the R package `VIM`; Templ et al. (2017)), giving first hints whether the missing completely at random (MCAR) assumption holds.

**Type of missingness** Missing at random (MAR) is assumed, and data will be imputed applying multivariate imputation by chained equations (MICE) using the R package `mice` (van Buuren and Groothuis-Oudshoorn (2011); van Buuren (2012)).

**Imputation model** Imputations for continuous data will be generated with the predictive mean matching method (pmm). For binary data a logistic regression model, for factors with more than two levels a multinomial logit model, and for ordered factors (>2 levels), an ordered logit model will be used.

**Predictor variables** For the analysis of **Research Question 1a** and the concomitant sensitivity analyses, the following variables will be used as predictors in the imputation process of missing values:

- EAT score obtained immediately after the effectiveness briefing (EAT\_1b)
- effectiveness briefing group (EXPBRIEF)
- side effects briefing group (SIDEBRIEF)
- EAT at baseline (EAT\_BL)
- gender (pers\_1\_2)
- age (age)
- duration of pain at first visit (painduration)
- pain bothersomeness at baseline (nrs\_1a\_2)
- depression (PROMIS\_BL\_depression.theta)
- CARE score (CARE\_1a\_red1)

For the analysis of **Research Question 1b** and the concomitant sensitivity analyses, the following variables will be used as predictors in the imputation process of missing values:

- pain intensity measured at the end of the acupuncture treatment (nrs\_8\_1)
- effectiveness briefing group (EXPBRIEF)
- side effects briefing group (SIDEBRIEF)
- pain intensity at first visit (screeningb\_1a\_4a)
- baseline optimism (LOT\_BL\_optim)
- baseline pessimism (LOT\_BL\_pessim)
- acupuncture therapist (acupuncturist)
- gender (pers\_1\_2)
- age (age)
- duration of pain at first visit (painduration)
- pain bothersomeness at baseline (nrs\_1a\_2)
- depression (PROMIS\_BL\_depression.theta)
- CARE score (CARE\_1a\_red1)

**Variables that are functions of other (incomplete) variables** There is no transformation, combination, or recoding of any variable involved. Hence, no passive imputation or post-processing of imputed values is required.

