## **8.4 Data Collection and Follow-up for Withdrawn Participants**

We will assess possible reasons for withdrawal or dropout at the last visit before dropout. A follow-up of withdrawn patients is not intended.

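### The SAP omits the protocol's comparison of imputation methods without explanation, and no planned analysis of 1b examines departures from missing at random

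*Combined protocol and SAP*

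**What the plan says.** Protocol 11.3.2 lists three kinds of sensitivity analysis for both 1a and 1b: (a) added covariates, (b) a per-protocol population, and (c) "using different multiple imputation methods for missing data (hot deck and regression methods").

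SAP 6.4 carries (a) and (b) forward and adds two analyses for 1b, one without opioid users and one restricted to patients with at least 6 of 8 sessions. Item (c) does not appear, and neither SAP 6.4 nor the revision history in SAP 1.4 explains why.

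SAP 6.5 states "Missing at random (MAR) is assumed" and sets one imputation procedure: chained equations, predictive mean matching for continuous variables, 50 imputed data sets. Its only look at the missingness mechanism is a set of tables and plots aimed at missing completely at random.

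Protocol 8.4 states "A follow-up of withdrawn patients is not intended", and Protocol 9.2.5 repeats this. Reasons for dropout are collected by questionnaire, but later pain is not. SAP 4.2 says that a few patients stopped acupuncture early and gives no number.

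**The concern.** There are two separate gaps.

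1. **The imputation model.** The protocol promised to show whether the 1a and 1b results depend on the imputation method. The SAP removes that comparison without recording it as a change. Protocol 13.1 requires changes to be laid down in an amendment. SAP version 1.0 is dated 29 May 2018, after the last patient visit on 11 December 2017, so a stated reason is all the more useful.

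2. **The missing-at-random assumption for 1b.** A patient who leaves before the end of treatment has no week-4 pain score and is not followed. If such patients have more or less pain than their observed data predict, every planned 1b analysis can miss it. A reader could not tell how large a departure would change the conclusion. The stated power for 1b is only 56-65%, so moderate shifts could matter.

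**Working it through.** **Planning figures first.** Inputs: two-sided alpha of 0.05 (SAP 4.1: "All tests are two-sided and performed at a significance level of 0.05"), 64 or 75 patients per briefing arm, and the 1b effect size (Protocol 11.2: "that resulted in an SMD of .38").

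- 1b power by two-sample t-test at SMD 0.38: 56.9% with 64 per arm and 63.8% with 75 per arm. The normal approximation gives 57.5% and 64.3%. The plan says "With the above mentioned sample we will have a power of 56-65% (n=128-150"), which is reproduced.
- 1a at SMD 0.5 and 80% power: 64 per arm, so 128 in total, as stated.
- Enrolment: 128 / 0.85 = 150.6, or 151, against "Assuming a dropout rate of approximately 15%, we sought to enroll 150 patients". This agrees within rounding.

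The point therefore does not rest on an error in the planning figures.

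**What each planned 1b analysis varies.**

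| Analysis | What changes | Examines departures from missing at random? |
|---|---|---|
| Primary (SAP 6.2.2, 6.5) | nothing; assumes missing at random | no |
| Complete cases (SAP 6.4.1) | drops incomplete patients | no |
| No opioid users (SAP 6.4.2) | population | no |
| At least 6 of 8 sessions (SAP 6.4.2) | population | no |
| Extended model (SAP 6.4.3) | covariates, with imputation | no |
| Protocol item (c), not carried forward | imputation method | normally no |

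**Size of a departure.** Let d be the share of an arm with week-4 pain missing. Let δ be the amount by which those patients' pain is worse than the imputation model predicts. Write H for the high and R for the regular briefing arm, and define benefit as pain in R minus pain in H. Approximately:

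error in estimated benefit = d_H × δ_H − d_R × δ_R

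The documents give no SD for week-4 NRS pain, so SD = 2 is an assumption. They give no missing share either. 15% is the planning dropout rate, and 5% is an assumed lower case. With a shift in one arm only:

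| Missing per arm | δ (NRS points) | Error (points) | Error (SD) | Share of 0.38 |
|---|---|---|---|---|
| 5% | 1 | 0.05 | 0.025 | 7% |
| 5% | 2 | 0.10 | 0.05 | 13% |
| 15% | 1 | 0.15 | 0.075 | 20% |
| 15% | 2 | 0.30 | 0.15 | 39% |

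- SD from 1.8 to 2.4, 15% missing, 1 point: 0.15/1.8 = 0.083 to 0.15/2.4 = 0.063 SD.
- Equal missingness and equal shift in both arms: 0.15 × 1 − 0.15 × 1 = 0.
- 10% missing in H and 20% in R, common 1-point shift: 0.10 − 0.20 = −0.10 points, or 0.05 SD (13% of 0.38), reducing the estimated benefit.

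**Consequence at 64 per arm.** If the effect is attenuated by 0.075 SD, t-test power falls from 57% to about 40%; by 0.15 SD, to about 25%. If there is truly no effect, errors of 0.075 and 0.15 SD raise the two-sided rejection rate from 5% to about 7% and 13%.

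**Imputation predictors.** The 1b list in SAP 6.5 includes baseline pain but not week-2 pain (nrs_4_1), which is collected after session 4. The list for the follow-up analysis in SAP 6.6.5 does include the end-of-treatment pain score.

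**The case against.** The strongest case against has four parts.

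- **Little is lost with item (c).** Predictive mean matching uses a regression model to select observed donor values, so it already combines ideas from both named methods. Protocol 11.3.6 also foresaw a more detailed plan. This stands as to practical effect. The undocumented change remains.
- **The missing share may be small.** SAP 4.2 speaks of a few early stoppers, and 15% was only an enrolment allowance. At 5% missing the 1-point shift is 0.025 SD. Even 0.075 SD is less than half a standard error of the SMD (about 2/√150 = 0.16). This stands and limits the size of the point.
- **The SAP has other safeguards.** It will report missing counts by group (SAP 5.5), the fraction of missing information and the share of variance due to missing data (SAP 6.5). These show how far the result leans on imputation, but not what happens if missing at random fails.
- **The arm-specific mechanism points the other way.** A reader might infer that the briefings bias 1b in favour of the high briefing. Protocol 8.2.3 has worsening patients in the regular arm told that they might not respond, but the same sentence asks them to be patient. If they did leave with worse pain than predicted, the regular arm would look too good and the benefit would be understated. The mechanism would, if anything, attenuate the effect.

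A reader might also infer that week-4 scores are missing mainly because patients stopped, or that dropouts have more pain. Neither is documented. Nor do the documents show that item (c) was dropped because of the data; SAP 3.1 says the analysis is blind to allocation.

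**Conclusion.** Both gaps are real, and they are separate. Item (c) is missing from the SAP without a reason, which affects 1a and 1b. Departures from missing at random are not examined in any planned 1b analysis. A reader might infer that dropping item (c) removed a check of missing at random. It did not, because both named methods normally make the same assumption; what was lost is a comparison of imputation models.

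For a 1-point shift in one arm only, the error is about 0.025 SD at 5% missing and 0.075 SD at 15% missing, or 7% to 20% of the planned 0.38. It is zero when shift and missingness are equal in both arms. These figures rest on an assumed SD of 2, an assumed shift and an assumed missing share, and the direction could be either way. This is a worthwhile, inexpensive improvement, not evidence that the 1b result is biased.

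**What to change.** 1. In SAP 6.4, restore a second imputation method for 1a and 1b, or record its removal as a deviation from Protocol 11.3.2 with the reason. Describe it as a check of the imputation model.
2. In SAP 6.4, add an exploratory delta-adjusted analysis for 1b. For example, add 0.5, 1, 1.5 and 2 NRS points to imputed nrs_8_1 values in the high arm only, in the regular arm only, and in both. Refit the SAP 6.2.2 model, pool, and report the delta at which the 1b conclusion changes.
3. Add week-2 pain (nrs_4_1) to the 1b imputation predictors in SAP 6.5. This makes missing at random more plausible for patients who leave after session 4.

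The cost is a few extra runs of the existing mice code and a short table. Items 1 and 2 fall under the SAP's rule that sensitivity results are exploratory, so the error rate of the primary tests is unaffected. Item 3 changes the primary imputation model and should be fixed before the allocation is known to the statisticians.
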